In the study area, a substantial number of pregnant women access care at family welfare clinics and community clinics within the governmental health system. Antenatal care typically comprises the measurement of blood pressure, height, weight, fundal height; anemia assessment; the provision of vitamin and mineral supplementation; management of common illnesses; counseling; and referral, if needed. On the basis of these guidelines, pregnant women with complications are referred to a subdistrict (Upazila) hospital, where basic laboratory services as well as delivery services including cesarean sections are typically available. Some patients utilize tertiary care health facilities for delivery or when identified with complications during pregnancy. Women may also access private health care, where they are likely to receive ultrasound scans and laboratory tests. Most private hospitals perform cesarean sections. Several private and NGO-run facilities are also engaged in providing maternal and child health services in the study area.

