#### Cluster Level

All government-run community clinics and family welfare clinics routinely providing antenatal care, delivery, or postnatal care services outside the referral health facility in the Matlab North and Matlab South Upazilas were eligible for the trial. Facilities were excluded if (1) there was no community health care provider or family welfare visitor to provide information on antenatal care visits in the previous month or (2) they reported fewer than five antenatal care visits in the previous month. Of the 72 health facilities in the study area, 59 (82%) were randomized (Figure 1). In total, 30 health facilities and 59 health workers were allocated to the intervention arm, whereas 29 health facilities and 64 health workers were allocated to the control arm (Figure 1).

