#### Intervention Arm

In the intervention arm, the eRegistry supported 3 data-driven DHIs linked to the digital client health records (Table 1) as follows: (1) for facility-based staff, health worker clinical decision support based on national guidelines to promote the correct management of health conditions identified in antenatal care; (2) for both field- and facility-based staff, feedback dashboards tracking the health worker’s progress toward pregnancy registration, antenatal care attendance and utilization, and clinical screening and management targets; and (3) for pregnant women, targeted client communication in the form of SMS text messages to address gaps in the timely attendance of antenatal care visits and facility delivery. Following the initial implementation of the eRegistry, the DHIs in the intervention arm were gradually introduced over the course of the trial; health worker clinical decision support was introduced in October 2018; targeted client communication via SMS and feedback dashboards were implemented in June 2019. Digital client health records were accessible across the cadres of health workers, facilities, and arms of the health system for a comprehensive longitudinal tracking of clients’ health status and services received (Table 1).

Guideline-based clinical decision support and feedback dashboards were developed in close collaboration with health workers. The decision support comprised referral and counseling reminders, medication alerts, and scheduling based on the recommended guidelines in the public health system. Feedback dashboards were customized for each cadre of health workers, with indicators of antenatal care attendance and screening and management of gestational diabetes, hypertension, and anemia. Targeted client communication included SMS text message reminders of routine antenatal care, referral facilitation SMS text messages for those at risk, and facility delivery reminders for those who are advised to have an institutional delivery. All DHIs were triggered by data entry into the eRegistry at the point of care by the health workers.

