Facility delivery among those advised to deliver in a facility	Case records in the eRegistry Postpartum household survey	Registrations continuously at point of care Household visit after completion of pregnancy	Proportion of women that deliver in a facility among those that should delivery in a facility based on certain risk factors identified during ANC	Health worker clinical decision support Targeted client communication via SMS text message: high risk, facility delivery reminders
Births with severe morbidity or mortality among all women and among those with any risk identified	Case records in the eRegistry Postpartum household survey	Registrations continuously at point of care Household visit after completion of pregnancy	Proportion with a very preterm birth, very low birth weight, perinatal death, or hospitalization of the newborn for at least 7 days after birth among all women enrolled in the trial, and those with any identified risk during ANC	Health worker clinical decision support Targeted client communication via SMS text message: referral reminders
Severe postpartum anemia	Postpartum household survey	Household visit after the completion of pregnancy	Proportion of women with severe anemia in postpartum	Health worker clinical decision support Targeted client communication via SMS text message: referral reminders

^a^ANC: antenatal care.

^b^eRegistry: electronic registry.

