#### Individual Women Within the Trial

The family welfare assistant enrolled individual women in the trial at pregnancy identification and registration. At that time, women were required to provide informed consent to receive communication from the study team and a home visit 8-14 days after the birth of the child (Figure 2). Women were then asked about their preferred public health facility for antenatal care, which determined allocation to an intervention or control cluster (Figure 3). Women may also be first identified as pregnant at a health facility. At this contact, women were registered in the eRegistry and automatically assigned to an intervention or control cluster based on the allocation status of that health facility (Figure 3). After completion of the pregnancy, the data collection team conducted a postpartum home visit within 8-14 days of birth for collection of outcome data.

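### The secondary newborn composite mixes three health states with a hospital stay of at least 7 days, which the intervention could increase through better access to care; add a version without that component

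*Protocol article*

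**What the plan says.** Table 3 (Outcomes) lists the secondary outcome "Births with severe morbidity or mortality among all women and among those with any risk identified". Its definition is "Proportion with a very preterm birth, very low birth weight, perinatal death, or hospitalization of the newborn for at least 7 days after birth", taken over all enrolled women and over those with a risk identified in antenatal care. Each component counts equally in one yes/no proportion. The row names decision support and SMS referral reminders as the parts of the intervention assumed to act on it.

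Under Intervention Arm, the SMS component includes "referral facilitation SMS text messages for those at risk, and facility delivery reminders for those who are advised to have an institutional delivery". On the health worker side, "The decision support comprised referral and counseling reminders, medication alerts, and scheduling based on the recommended guidelines in the public health system". The control arm has neither. Under Study Setting, "pregnant women with complications are referred to a subdistrict (Upazila) hospital".

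Table 3 also treats completed referral as a favourable outcome, and facility delivery likewise: "Proportion of women that deliver in a facility among those that should delivery in a facility based on certain risk factors identified during ANC".

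**The concern.** Very preterm birth, very low birth weight and perinatal death describe what happened to the child. A long stay describes both how ill the child was and whether the child got into a hospital. If the package moves at-risk women toward hospital care, some sick newborns who would not have been admitted may be admitted and kept. One row of Table 3 would then score as severe morbidity an event that success on other rows makes more likely.

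Blinded data collection at the home visit does not help, because the difficulty is what the event means and not how it is recorded. At stake is the reading of the trial's only newborn health outcome: a null or adverse result could reflect no benefit, or a benefit offset by more admissions, and the four-part proportion alone does not say which.

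**Working it through.** **The plan's own figure.** The only design figure is power above 80% for the two primary outcomes. Inputs: "Of the 72 health facilities in the study area, 59 (82%) were randomized" (30 and 29 per arm), 77 women per cluster, ICC 0.1, and two-sided alpha 0.05 (assumed, as none is stated). Design effect = 1 + (77 - 1) x 0.1 = 8.6. Effective n per arm = 29 x 77 / 8.6 = 260, or 269 with 30 clusters. Power is 92-93% for 20% vs 33% and 86-87% for 12% vs 22%. The stated figure is reproduced, and this point does not touch it.

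**What the definition does, without any rates.**
- A newborn who would have died perinatally but reaches hospital, survives and stays 7 days is an event either way, so the averted death earns no credit.
- A sick newborn who would have survived without admission is a non-event; admitted for 7 days, the same child becomes an event.
- A very preterm or very small newborn is already an event; a long stay adds nothing.
- A newborn whose illness is prevented by better antenatal care moves from event to non-event.

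The first two patterns hide benefit or suggest harm, and the last shows benefit. The direction of the component is ambiguous.

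**Illustration of the mechanism (all rates assumed).** Let a be the proportion with very preterm birth, very low birth weight or death, h the proportion counted only through a long stay, RR the true effect on a, and u the ratio by which access changes h. Control = a + h; intervention = a x RR + h x u. The benefit is cancelled at u = 1 + a(1 - RR)/h.

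With a = 4%, h = 2% and RR = 0.80, control is 6.0%:

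| u | Intervention | Composite RR |
|---|---|---|
| 1.0 | 3.2% + 2.0% = 5.2% | 0.87 |
| 1.2 | 3.2% + 2.4% = 5.6% | 0.93 |
| 1.5 | 3.2% + 3.0% = 6.2% | 1.03 |
| 2.0 | 3.2% + 4.0% = 7.2% | 1.20 |

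Without hospitalization the comparison is 4.0% vs 3.2%, RR 0.80, in every row. Break-even u is 1 + 0.8/2 = 1.4; it is 1.8 at h = 1% and 1.27 at h = 3%. With RR 0.70 the three values are 2.2, 1.6 and 1.4 (h = 1%, 2%, 3%).

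**How large the access effect might be (also assumed).** Suppose long stays follow 3-5% of facility births and 0.5-1% of home births, and facility delivery rises by 10-15 points among women who are sent reminders. Added events among those women: 0.10 x (0.03 - 0.005) = 0.25 points, to 0.15 x (0.05 - 0.01) = 0.60 points. If 20-50% of all women are advised to deliver in a facility, the excess over all women is 0.20 x 0.25 = 0.05 to 0.50 x 0.60 = 0.30 points. Overlap with the other components is not subtracted, so these figures lean high.

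**Against sampling error.** With 59 x 77 = 4,543 women and a 6% event rate (assumed), the 95% half-width for the difference is 1.96 x sqrt(2 x 0.06 x 0.94 / 2,271.5) = 1.4 points without clustering. At an assumed ICC of 0.01 (design effect 1.76) it is 1.8 points. With all of the roughly 8,000 registrations it is 1.0 to 1.6 points.

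**The case against.** The strongest reply is that the mechanism is inferred. No section says the intervention changes newborn admission. Referral success is defined as extra care in pregnancy, the description of the subdistrict hospital does not mention newborn inpatient care, and the composite's own row does not list facility delivery reminders. Better antenatal care could also shorten or prevent long stays. This stands as a limit on certainty: the claim is that the component could rise, not that it will. The reminders are nevertheless part of the same randomized package.

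The 7-day threshold already excludes routine stays after birth, and hospitalization is the only marker of severe illness in surviving newborns who are neither very preterm nor very small. Both points stand and are reasons to keep the registered composite.

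Facility delivery and completed referral are reported separately, so readers can see whether access rose. That helps, but it does not show whether additional long stays came from access or from illness.

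Components by arm may be planned in an analysis plan that is not shown. Their absence from an article is not the point; the point is the definition fixed here and how a result on it will be read.

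A reader might infer that most or all of a real benefit would be masked. The documents do not support that. They give no component rates, reminders reach only women advised to deliver in a facility, part of the long stays would fall on newborns already counted, and full cancellation in the illustration needs long stays to rise by a factor of at least 1.27.

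**Conclusion.** The point holds as a matter of interpretation for one secondary outcome. The composite contains a component whose direction is ambiguous under an intervention that promotes referral and facility delivery, so it could dilute a benefit or suggest harm. This is most plausible among women with an identified risk, where the prompts are concentrated. The size cannot be derived from the documents. Under the assumptions shown, the excess over all women is 0.05 to 0.30 points, against a half-width of at least 1.0 point; a subgroup would have a wider interval still. Neither a stated fraction of benefit lost nor a claim that the composite is unusable is warranted. The conclusions on the two primary outcomes are unaffected.

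**What to change.** Keep the registered four-part composite as the defined secondary outcome. Add, for all women and for those with an identified risk:
- a prespecified sensitivity composite of very preterm birth, very low birth weight or perinatal death;
- each of the four components by arm, with the stay of at least 7 days also labelled as use of care;
- a reading rule: a null or adverse four-part result is not interpreted as lack of benefit or as harm to newborns unless the version without hospitalization agrees.

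Statistical Methods has the code written on dummy allocations and a separate statistician run the final analysis, so this can be fixed before actual allocation is applied. No new data are needed. The cost is one extra analysis with fewer events and less precision, plus a few table rows. It should be declared as an addition to the registered outcome; Protocol Amendments already describes how changes to secondary outcomes are recorded.

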#### Individual Level

Individual women with a confirmed pregnancy were registered, and their health data were entered into the eRegistry. Pregnancy identification and registration may be conducted by family welfare assistants or health assistants at the households or by community health care providers or family welfare visitors at the women’s first health facility encounter. All pregnancies identified by a health worker using the eRegistry should be entered into the system. Only women who consent to have a household visit after birth were included in the trial because the outcome data were derived from the household survey.

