### Outcomes

The outcomes were formulated based on their relevance to the health system context and were meant to capture the potential effects of the specific DHIs under assessment. Data for the primary (Table 2) and secondary outcomes (Table 3) will be derived from the eRegistry’s client health records and through postpartum home visit interviews.

**Table 2 table2:** Primary outcomes, data sources, and definitions.

Primary outcome	Sources of data	Measurement sequence	Definition	Intervention subcomponents with most direct effect
Timely attendance at eligible ANC^a^ visits	Postpartum household survey	Registrations continuously at point of care Household visit after the completion of pregnancy	Proportion with timely attendance	Targeted Client Communication via SMS text message: ANC appointment reminders
Screening and management for hypertension in pregnancy	Case records from the eRegistry^b^	Registrations continuously at point of care	Proportion that has at least one ANC at a randomized health facility with: Blood pressure measurement at routine ANC visits, and Referred if blood pressure is high, or Referred if blood pressure is high outside of the routine ANC visit	Health worker clinical decision support Feedback dashboards with action items

^a^ANC: antenatal care.

^b^eRegistry: electronic registry.

**Table 3 table3:** Secondary outcomes, data sources and definitions.

Secondary outcome	Sources of data	Measurement sequence	Definition	Intervention subcomponents with assumed direct effect
Timely first ANC^a^ visit	Case records from the eRegistry^b^ Postpartum household survey	Registrations continuously at point of care Household visit after the completion of pregnancy	Proportion of women that have an ANC visit at or before 16 weeks among those with a home pregnancy registration before 16 weeks	Targeted Client Communication via SMS text message: ANC appointment reminders
High-risk women successfully referred to a skilled provider for additional care	Case records from the eRegistry Postpartum household survey	Registrations continuously at point of care Household visit after the completion of pregnancy	Proportion of women that received additional care during pregnancy among those that are referred for severe anemia, or hypertension or diabetes during pregnancy	Health worker clinical decision support Targeted client communication via SMS: Referral reminders, high risk, facility delivery reminders

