### Data Collection

#### Overview

The eRegistry used by health workers in the intervention and control arms will provide some of the data for outcome measurements. Independent trained project staff collected data regarding birth outcomes, antenatal care utilization, and referral care seeking from a subset of the population of registered pregnancies through a postpartum household survey. The postpartum household survey started in June 2019, 8 months after the commencement of recruitment. Data collectors were provided with a list of all pregnancies registered in the eRegistry that were beyond 28 weeks of gestation at a given point in time. The data collectors made biweekly phone calls to clients from 28 to 35 weeks, and weekly thereafter to ascertain whether the pregnancy was ongoing. Postpartum household visits for data collection were conducted within 8-14 days of childbirth. A paper-based structured questionnaire was used for data collection (Multimedia Appendix 1), focusing on the experiences of pregnancy and childbirth, health care interventions received, and health outcomes of the mother and the newborn. The infant’s weight was measured during the home visit; weight was measured in minimal clothing, and the weight of the clothes was subtracted from the total weight. Where possible, women’s finger-prick blood was used to measure hemoglobin. The questionnaires were checked for completeness and consistency by the data collectors’ supervisors, and women were interviewed again if needed. Data from the paper questionnaires are being made electronic, and consistency checks are performed by the study team after data entry.

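### The birth composite counts all enrolled women whenever they registered, so any difference between arms in registration timing would bias it, in either direction

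*Protocol article*

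**What the plan says.** In the protocol's Outcomes section, Table 3 gives the composite as a simple proportion, worded thus: "very preterm birth, very low birth weight, perinatal death, or hospitalization of the newborn for at least 7 days after birth among all women enrolled". A second version is taken among women with a risk identified during antenatal care. Neither denominator depends on when the woman was registered.

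Entry is open-ended. Under Eligibility Criteria, Individual Level: "Individual women with a confirmed pregnancy were registered, and their health data were entered into the eRegistry". The only further condition there is consent to the home visit. Under Allocation: "Women may also be first identified as pregnant at a health facility", in which case that facility decides her arm.

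The Intervention Arm section describes "feedback dashboards tracking the health worker’s progress toward pregnancy registration" among other targets, for both field and facility staff. Table 1 shows dashboards in the intervention column only. They came late: "targeted client communication via SMS and feedback dashboards were implemented in June 2019".

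For birth outcomes, data collectors worked from a "list of all pregnancies registered in the eRegistry that were beyond 28 weeks of gestation at a given point in time" (Data Collection, Overview).

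The same Table 3 does condition another outcome, the timely first antenatal visit, on registration time: "among those with a home pregnancy registration before 16 weeks".

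**The concern.** This is left truncation. An early event is counted only if the woman is already registered when it happens, and a late entrant has by definition passed the early weeks without one. Late entrants therefore add structural zeros for very preterm birth, for early stillbirth and, largely, for very low birth weight. A simple proportion over all enrolled women ignores time of entry.

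The zeros do no harm to the ratio if both arms register women at the same gestations. Here that is not secured by design, because enrolment follows randomisation and one arm has a tool aimed at registration. If the tool moves registration times, the number of countable early events changes with no change in risk. This is the only listed outcome covering perinatal death and severe newborn morbidity, so a timing artefact could be read as a clinical effect.

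**Working it through.** The protocol gives no event rate, intracluster correlation or power for this composite, so it has no figure to reproduce. Its stated power of more than 80% concerns the two primary outcomes and has no bearing here.

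**From the protocol:** 30 and 29 facilities; 77 women per cluster; enrolment October 2018 to June 2020 (21 months); dashboards from June 2019 (13 of those months); follow-up list from 28 weeks, so shifts in registration before 28 weeks do not matter.

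**Assumed:** very preterm births 1.5%, spread evenly over 28–32 weeks; stillbirths 2%, spread evenly over 28–40 weeks; other components 3%, unaffected by entry time; no overlap between components; everyone registered by 40 weeks; no true effect of the intervention.

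**Formula:** countable risk = event rate × average share of women already registered over the weeks in which the event occurs, with linear interpolation between the stated weeks.

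*Scenario A.* Registered by 28/32/36 weeks: control 85/92/97%, intervention 92/97/99%.
- Very preterm: control (0.85+0.92)/2 = 0.885; intervention (0.92+0.97)/2 = 0.945; ratio 1.068.
- Stillbirth: control (0.885+0.945+0.985)/3 = 0.938; intervention (0.945+0.980+0.995)/3 = 0.973; ratio 1.037.
- Composite: control 1.5×0.885 + 2×0.938 + 3 = 6.20%; intervention 1.5×0.945 + 2×0.973 + 3 = 6.36%; ratio 1.026.

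*Scenario B.* Control 70/80/92%, intervention 80/90/97%.
- Very preterm: 0.85/0.75 = 1.133.
- Stillbirth: control (0.75+0.86+0.96)/3 = 0.857; intervention (0.85+0.935+0.985)/3 = 0.923; ratio 1.078.
- Composite: control 1.5×0.75 + 2×0.857 + 3 = 5.84%; intervention 1.5×0.85 + 2×0.923 + 3 = 6.12%; ratio 1.049.

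**Opposite direction.** Exchanging the arms' timings gives 1/1.026 = 0.975 and 1/1.049 = 0.953. The sign follows the timing difference.

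**Dashboard period only.** If the shift applies to 13/21 of enrolment, the excess falls to 0.026×13/21 = 0.016 and 0.049×13/21 = 0.030, so ratios of about 1.016 and 1.030. This may dilute too much, because the household survey also began in June 2019.

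**A second model.** Let e be the risk of events confined to the very preterm window, o the risk of other events, and L the share registered after it. Arm risk = (1−L)(e+(1−e)o) + L·o. With e = 1.5% and o = 4%, the bracket is 0.0544.
- L 20% in control against 10% in intervention: 0.8×0.0544 + 0.2×0.04 = 5.15% against 0.9×0.0544 + 0.1×0.04 = 5.30%; ratio 1.03.
- L 40% against 10%: 4.86% against 5.30%; ratio 1.09.
- Over e 1–3%, o 2–6% and late shares of 20–40% against 10–20%, unequal shares give 1.01 to 1.23. The top needs the most extreme value of every input. Equal shares give 1.00.

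**Simulation.** With mean registration 3 to 6 weeks earlier in the intervention arm, the ratio was 1.01 to 1.06. Counting only women registered before 28 weeks brought it to 0.997–1.003, with timing simulated as independent of risk.

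**Against sampling error.** At a 6% rate with 30×77 = 2310 and 29×77 = 2233 women, the standard error of the log ratio is √(0.94/(0.06×2310) + 0.94/(0.06×2233)) = 0.117. An assumed intracluster correlation of 0.02 multiplies it by √(1+76×0.02) = 1.59, giving 0.187. The undiluted bias is then between ln(1.026)/0.187 = 0.14 and ln(1.049)/0.117 = 0.41 standard errors.

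**The case against.** The strongest objection is that the protocol never shows timing to differ. At home, registration comes first and the preferred-facility question then fixes the arm. The Blinding section says the community workers doing this did not know that facility's status. Decision support and SMS messages are triggered by data entry, so they cannot bring forward the registration that precedes them. Only the dashboards remain, and they began in about month 9 of 21. This weakens the mechanism but does not remove it: facility staff were unblinded and can register women, and Table 1 lists dashboards for community cadres in the intervention arm only.

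A reader might infer that the composite will show false harm. The documents do not support that. They say that the dashboards track progress toward registration, not that registration becomes earlier. A push for more registrations could bring in late pregnancies and reverse the sign.

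A reader might also infer that the headline should move to early registrants. That does not follow either. Registration timing arises after randomisation, so restricting on it compares women who may be differently selected and departs from the planned intention-to-treat analysis. This objection stands and shapes the fix.

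The adjustment rule under Statistical Methods is not a clear safeguard. It acts only when the effect measure changes by more than 5%, and the composite distortions in scenarios A and B (2.6% and 4.9%) fall below that. Gestational age at registration is not among the listed background characteristics.

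An analysis plan that is not shown may add a sensitivity analysis. The denominator itself, however, is fixed explicitly in the article.

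**Conclusion.** The point holds as a conditional weakness. The denominator, the open-ended entry and the registration tool confined to one arm are all in the text. Together they let a difference in registration timing pass into the composite ratio.

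The likely size is modest: about 1.03 to 1.05 if the intervention arm registers earlier under scenarios A and B, about 1.02 to 1.03 if only the dashboard period is affected, below 1 if the arm gains late registrants, and no bias in the ratio if timing is equal. That is well under one standard error of the composite. The larger ratios of 1.07 to 1.13 belong to very preterm birth alone.

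All rates and timings are assumptions, as is 32 weeks for the very preterm limit. The direction for a given timing difference does not depend on that limit.

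**What to change.** Keep the all-enrolled intention-to-treat proportion as the headline. Prespecify one companion analysis: either gestational-age-specific risk with delayed entry at registration, or the same composite limited to women registered before 28 weeks, where the follow-up list starts. Report gestational age at registration by arm. State that a difference in the all-enrolled composite will not be read as benefit or harm unless the companion analysis agrees.

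This is analysis-plan wording, using registration dates and gestational ages that the eRegistry should already hold. The costs are a little more analysis work and, if restriction is chosen, fewer women: those not registered by 28 weeks, which is 8–15% by arm in scenario A and 20–30% in scenario B. Delayed entry keeps everyone. Both analyses assume that registration timing is unrelated to underlying risk, and the report should say so.
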